## Abstract

**Background:**

Palliative care focuses on supporting patients diagnosed with advanced, incurable disease; it is ‘family centered’, with the patient and their family (the unit of care) being core to all its endeavours. However, approximately 30–50 % of carers experience psychological distress which is typically under recognised and consequently not addressed. Family meetings (FM) are recommended as a means whereby health professionals, together with family carers and patients discuss psychosocial issues and plan care; however there is minimal empirical research to determine the net effect of these meetings and the resources required to implement them systematically.

The aims of this study were to evaluate**:** (1) if family carers of hospitalised patients with advanced disease (referred to a specialist palliative care in-patient setting or palliative care consultancy service) who receive a FM report significantly lower psychological distress (primary outcome), fewer unmet needs, increased quality of life and feel more prepared for the caregiving role; (2) if patients who receive the FM experience appropriate quality of end-of-life care, as demonstrated by fewer hospital admissions, fewer emergency department presentations, fewer intensive care unit hours, less chemotherapy treatment (in last 30 days of life), and higher likelihood of death in the place of their choice and access to supportive care services; (3) the optimal time point to deliver FM and; (4) to determine the cost-benefit and resource implications of implementing FM meetings into routine practice.

**Methods:**

Cluster type trial design with two way randomization for aims 1-3 and health economic modeling and qualitative interviews with health for professionals for aim 4.

**Discussion:**

The research will determine whether FMs have positive practical and psychological impacts on the family, impacts on health service usage, and financial benefits to the health care sector. This study will also provide clear guidance on appropriate timing in the disease/care trajectory to provide a family meeting.

**Trial registration:**

Australian New Zealand Clinical Trials Registry ACTRN12615000200583.

## Background

Acute hospitals provide end-of-life care to the majority of people who die in Australia and many other countries [1]. Palliative care focuses on supporting patients diagnosed with advanced, incurable disease. It is ‘family centered’, with the patient and their family considered to be the unit of care [2]. Given the significant burden associated with caring for a dying relative, the World Health Organisation (WHO) advocates that health care services focus on enhancing family members’ quality of life [3]. Accordingly, many nations have established standards and policies for responding to the needs of family carers as well as patients [4–6]. Despite these initiatives, patients with advanced disease may be exposed to aggressive or futile treatment, and approximately 50 % of carers experience psychological distress, which is typically under-recognised [7].

Communication with patients and their family is a vital element of palliative care. Information exchange, preparing for discharge and assessing needs is recommended standard practice. Only when carers of patients with advanced disease are well informed are they able to provide high quality end-of-life care for their relative [8]. Inadequate communication can have profound negative effects resulting in psychological distress due to unmet information needs, lack of shared decision making and mistrust of healthcare providers [9]. Open discussions between health professionals and family carers are an effective way of providing psychological support [10]. However, the quality of communication can vary considerably and communication failures are the most common reason for complaints in health care, with end-of-life care being no exception [1]. Interventions with family carers which focus on responding to needs and preparing them for their role have produced demonstrable improvements in carer well-being and sense of preparedness [11, 12], reduction of unmet needs [11, 13–16], and carer burden and increased quality of life and knowledge of patient symptoms [17]. Findings from systematic reviews also demonstrate that structured information from health professionals can reduce anxiety [18]. The benefits of family carer involvement in discharge planning have also been reported [19].

One of the most important clinical tools for healthcare providers to facilitate communication for people with advanced disease is a family meeting [20–22]. Family meetings (also known as family conferences), are meetings between the family carers, the patient (where possible) and health care professionals, and are undertaken for multiple purposes including psychosocial support, clarifying the goals of care, discussing diagnosis, treatment, prognosis, discharge planning and developing a plan of care for the patient and carer [23]. Studies on family meetings in intensive care units (ICUs) have demonstrated improvement in communication [20, 24], decrease in carer burden [25], and, importantly, reduction in length of stay [26]. Family meetings in the ICU have also led to measurable benefits including decreased post-traumatic stress disorder, anxiety and depression [20, 27].

Family meetings are recommended as a core intervention within the context of palliative care provision [28]. These encounters, however, are not usually provided consistently or systematically, nor are they conducted according to best available evidence [29]. Moreover, the specific outcomes for patients, family carers and health professionals associated with conducing a family meeting within the palliative care setting are underexplored.

### Structured family meetings guidelines and pilot work

[name] and colleagues developed clinical practice guidelines [30] for conducting Structured Family Meetings (SFMs) for those patients referred to specialist palliative care in hospitals.

The meetings are intended to take no longer than one hour and should be conducted by health care professionals with relevant training in facilitating such meetings. [name] and colleagues subsequently examined the feasibility and effectiveness of the SFM clinical guidelines in an observational study using mixed methods evaluation [31]. The following outcomes were demonstrated: (1) family carers reported significant reductions in unmet needs; (2) family carers reported that meetings were informative and useful; (3) health professionals reported that the meetings were well-facilitated and (4) family meeting facilitators (provided with specific training to convene and conduct a family meeting) reported that they were better equipped to facilitate the meetings. This study provided preliminary data on the feasibility and acceptability of family meetings as a means of identifying and addressing family concerns. These findings require further testing in a larger sample, using more robust research methods [31]. In addition, it would be advantageous to explore patient outcomes, ascertain any sustained longer term benefits of SFM for family carers (focusing on distress) and discern the best time (within the advanced disease trajectory) to conduct family meetings.

In summary, whilst current guidelines advocate family meetings be routinely conducted for all patients [28], these encounters are typically neither consistently provided nor conducted according to best available evidence. There is therefore justification to further investigate, within a robust research evaluative study design, the impacts and outcomes of SFM for patients, carers and families and the barriers and enablers that may influence effective implementation. Given the major financial and resource implications of SFM, we will also provide clear guidance on the appropriate timing in the disease/care trajectory to provide a family meeting.

The purpose of this project is to evaluate outcomes for patients and family carers who attend a SFM and determine the cost and resource implications of implementing SFM into standard practice for hospitalised patients with advanced disease.

Our aims are:To assess the short and longer term effect of SFM on patient and family carer outcomes and determine the most appropriate time point in a patient’s advanced disease trajectory to provide a SFM.To determine the cost-benefit and resource implications of implementing SFM meetings into routine practice.

## Methods

The following sections detail the methods for addressing each of the project aims.

### Aim 1

To assess the short and longer term effect of SFM on patient and family outcomes and determine the most appropriate time point in a patient’s disease trajectory to provide a SFM.

Our alternative hypotheses for Aim 1 are:(H1) Family carers of hospitalised patients with advanced disease (referred to a specialist palliative care in-patient setting or palliative care consultancy service) who receive a SFM will report significantly lower psychological distress (primary outcome), fewer unmet needs, increased quality of life and feeling more prepared for the caregiving role.(H2) Patients who receive the SFM will experience appropriate quality of end-of-life care, as demonstrated by fewer hospital admissions, fewer emergency department (ED) presentations, fewer intensive care unit hours, less chemotherapy treatment (in last 30 days of life), and higher likelihood of death in the place of the person’s choice (in consultation with their caregivers) and access to supportive care services.(H3) Patients and family carers who receive a SFM earlier in their advanced disease trajectory (i.e further way from death) will have more favourable outcomes (as per outcomes listed in H1 and H2).

#### Research design

This study will randomise three participating sites: all sites will collect baseline data (i.e. Time 1, 2 & 3 data) for 6 months; then two of the three sites will deliver the intervention. As such, one site will remain the control site for the entire time and there will be before and after measurements (with excellent baseline data collected prospectively) for the two sites which will participate in the intervention. As each site will have baseline data, any differences between sites can be identified and, if necessary, controlled for during the analyses. The intervention recruitment period is longer than the control period in the two intervention sites to ensure that the total numbers of control and intervention participants are approximately equivalent). This design was deemed the most appropriate and feasible method for this type of health service research, since randomisation by patient in each service risks cross-group contamination within that clinical setting. A conventional cluster trial or stepped-wedge design is not feasible due to the significant number of sites that would be required. Sites will be randomised by an independent statistician via a random number generation system.

#### Participants

##### Inclusion criteria for patients

Hospitalised patients with advanced, non-curable disease referred to a specialist palliative care in-patient unit or palliative care consultancy service for inpatients, who have a person (relative or friend) whom they perceive to be their main support person (i.e primary family carer), who are willing for the research team to approach the family carer for potential research participation and agreeable to have their medical information shared with the family carer, if pertinent, during the SFM. *Exclusion criteria for patients:* Under 18; likely to die within 1 week (as assessed by treating physician or senior nurse); unable to identify a primary family carer, unable to provide informed consent due to cognitive impairment or incapacity to comprehend and speak English (as assessed by treating physician, senior nurse or research assistant).

##### Inclusion criteria for family carers

Nominated by the patient as their primary support person and willing to attend a SFM if allocated to the intervention arm.

##### Exclusion criteria for family carers

Under 18; incapacity to understand or speak English; unable to provide informed consent due to cognitive impairment (as assessed by the research assistant); or not agreeable to being considered the primary family carer.

For the intervention phase, patients and family carers who have already been involved in a formal family meeting as part of routine specialist palliative care will be excluded from participation. As part of routine data collection for the study we will ask each participating site to record in the medical record if a formal family meeting (ie specific meeting set up to confirm plan of care) has occurred.

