#### Standard care

Standard care is known to be quite heterogeneous. Family meetings are offered in all participating sites but the frequency and method of conduct varies; thus we are mindful that some control participants will receive a family meeting, although these are typically not formally structured. Our research has been designed in recognition of this and we will also collect data on the frequency of family meetings conducted in the control group.

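### A prior formal family meeting is an exclusion only in the intervention phase, so at least the baseline-phase controls enter under a looser rule than the intervention group they are compared with

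*Protocol article*

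**What the plan says.** The general carer exclusions cover age, language, capacity and, last, carers who are "or not agreeable to being considered the primary family carer". A separate paragraph under the same heading (Exclusion criteria for family carers) then removes a further group: "For the intervention phase, patients and family carers who have already been involved in a formal family meeting" within routine specialist palliative care. That paragraph also states that "we will ask each participating site to record in the medical record if a formal family meeting" has taken place. Neither the patient criteria nor the carer inclusion criteria contain a prior-meeting rule for other participants.

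Under Research design, "all sites will collect baseline data (i.e. Time 1, 2 & 3 data) for 6 months; then two of the three sites will deliver the intervention", and "one site will remain the control site for the entire time". Controls therefore come from two sources: the baseline phase at all three sites, and the later period at the one site that never delivers the intervention.

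Under Standard care the authors write that "we are mindful that some control participants will receive a family meeting, although these are typically not formally structured", and they plan to record how often this happens. Under Analyses plan, the main comparison pools intervention and control data across sites after a check for site differences at baseline. It uses a linear mixed model with a group-by-time test and between-group contrasts at Times 2 and 3. A sub-analysis comparing controls who had no meeting with intervention carers who had one is planned only if no intervention effect is found.

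**The concern.** A family that had a formal routine meeting before being approached can become a control in the baseline phase. The same family, arriving at the same hospital after the intervention has started, is turned away. Such families need not resemble the rest. The meeting may have been called because their needs were greater, or it may already have relieved some distress.

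The timing makes this harder to repair. In the two intervention sites the design relies on a before-and-after comparison, and the eligibility rule switches on at the same boundary as the intervention. Adjusting for site cannot separate the two changes. The trial has three sites and no individual randomisation, so randomisation does not balance a difference created at entry. At stake is a bias of unknown sign in the primary GHQ comparison that one sentence in the criteria would avoid.

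**Working it through.** **1. The plan's own figure, as a yardstick.** Inputs from the sample size section: two-sided alpha 0.05, power 90%, means 16.8 and 14 (difference 2.8), SD 6, equal groups.

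n per group = 2 × SD² × (1.960 + 1.282)² / difference² = 72 × 10.51 / 7.84 = 96.5, so 97. This reproduces the stated 97.

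The same section says that the calculation uses a difference of 2.4. That would need 72 × 10.51 / 5.76 = 131.4, so 132 per group; with 97 per group, power at 2.4 is about 80%. This mismatch is a separate matter. I use 2.4 below only as the stated target difference.

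**2. Who enters under which rule.**

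| Participants | Prior-meeting exclusion |
|---|---|
| Baseline phase, all three sites (controls) | Not stated |
| Continuing control site, later period (controls) | Not stated; applies only if the phase is a calendar period |
| Two intervention sites, later period (intervention) | Applies |

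**3. Share of controls under the looser rule (s).** Assume 24 months of recruitment (the two years in the feasibility paragraph) and equal accrual at each site.

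- Baseline controls: 3 sites × 6 months = 18 site-months.
- Control site afterwards: 1 × 18 = 18 site-months.
- Intervention: 2 × 18 = 36 site-months.

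Controls total 36, which fits the stated aim of roughly equal groups. So s = 18/36 = 0.5 if the control site applies the rule in the later period, and s = 1 if it never does.

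**4. Illustrative shift in the control mean.** Let p be the share of the loosely screened controls who had a prior meeting, and D the amount by which their GHQ differs from that of other carers. Neither is in the documents.

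Shift = s × p × D

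- Low: 0.5 × 0.10 × 2 = 0.1 points.
- Middle: p = 0.20, D = 4 gives 0.4 (s = 0.5) to 0.8 (s = 1), or 17% to 33% of 2.4.
- High: 1.0 × 0.30 × 5 = 1.5 points.

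**5. What a shift would do to the test.** With 97 per group and SD 6, SE = 6 × √(2/97) = 0.86. Take p = 0.20 and D = 2.8.

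- s = 1: shift 0.56. Under no true effect, two-sided rejection is about 10%. If the shift acts against the intervention, power at a true difference of 2.4 falls from about 80% to 57%.
- s = 0.5: shift 0.28, and 0.28/0.86 = 0.325. Rejection under no effect is P(Z > 1.635) + P(Z < −2.285) ≈ 5.1% + 1.1% = 6.2%. Power against an adverse shift is P(Z < 2.12/0.86 − 1.96), about 69%.

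Steps 4 and 5 ignore both Time 1 adjustment and clustering.

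**6. Whether the planned analysis absorbs it.** Site adjustment does not, because the rule changes within site. The group-by-time test removes a difference in level that is already present at Time 1 and stays constant. It does not remove a difference in later course. The sub-analysis on meeting status is conditional on finding no effect, and it also sorts carers by meetings held after enrolment, so it does not restore equal entry.

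**The case against.** The asymmetry is in the text, but several points limit what follows from it.

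- **The window is short.** Patients are approached within 48 hours of admission or of being seen by the consultancy service, and carers within 72 hours. Only formal meetings count, and the Standard care section says that "some control participants will receive a family meeting, although these are typically not formally structured". The share affected may be small. This stands, with one limit: about a third of admissions pass through both services, so some families could have had an earlier meeting.
- **The model removes part of it.** For the group-by-time test, the relevant D is a difference in change after Time 1, which could be much smaller than a difference in level. This stands. The protection is only partial if the planned contrasts at Times 2 and 3 are not adjusted for Time 1.
- **The phase may be a calendar period.** The control site would then apply the same rule in the later period, and concurrent controls would match. The wording allows this reading. The baseline-phase controls would still differ.

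A reader might infer that all controls were selected differently, that the bias favours the intervention because families met early are more distressed, or that it amounts to a known fraction of the planned effect. The documents support none of these. The first depends on the ambiguous phase. The second is conjecture, since an early meeting could equally have lowered distress. The third needs values of p and D that are not given.

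**Conclusion.** The point holds as an eligibility inconsistency. Followed as written, the plan compares an intervention group screened for prior formal meetings with a control group of which at least the baseline-phase part, about half under the assumptions on duration and accrual, is not. The change coincides with the start of the intervention and is not undone by the planned analysis.

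Its effect cannot be sized or signed from the documents. The 0.1 to 1.5 point range shows only what assumed inputs imply before Time 1 adjustment, and the lower part is plausible given the short recruitment window. This should be fixed because the remedy is simple and the bias avoidable; there is no demonstration that it would decide the result.

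**What to change.** State one rule for every site and both phases: patients and carers who have had a formal family meeting under routine specialist palliative care before enrolment are not eligible. Define the enrolment cut-off once, and say explicitly that the continuing control site applies it throughout.

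If baseline controls are already enrolled, restrict the primary comparison to participants with no formal meeting before enrolment, using the same cut-off in both groups. Report the unrestricted analysis as a sensitivity analysis. The cut-off should not be moved to Time 1 for controls only. Time 1 may fall up to a week after referral or admission, so that would be later than the point at which intervention families are screened and would create a new asymmetry.

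Record the date of each formal meeting. The article asks sites to note whether one occurred and to count meetings in controls, but does not mention dates, and the restriction depends on them.

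Keep controls whose meeting takes place after enrolment, since that is usual care.

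The cost is one sentence in the criteria, one date field, a screening check already needed in the intervention phase, and slightly fewer controls.

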#### Procedure

Recruitment (see Fig. 1) will occur as soon as possible (within 48 h) after the patient is admitted to the palliative care unit or seen by the consultancy service. The research assistant will screen the list of new admissions to both the inpatient unit and the consultative team daily and speak with the clinical team to check eligibility. They will approach eligible patients in person within 48 h of admission to give patients a copy of the Plain Language Statement and consent form and invite patients to participate. Patients will need to consent to their medical records being accessed and their medical details being discussed at the family meeting (if well enough and if allocated to the intervention group). Patients will need to identify a family carer (as per inclusion criteria) and provide consent for the research assistant to contact them about the study. Patients will not be required to provide any self-report data.

**Fig. 1 Fig1:**
[figure not shown]
Recruitment and data collection

The research assistant will then phone the family carer (or approach them in person at the hospital) to invite them to participate within 72 h of patient admission (see Fig. 1). The research assistant will give the family carer a copy of the Plain Language Statement and consent form if approaching them in person and go through it with them and obtain formal written consent. If contact has been made by phone, the research assistant will go through the content of the Plain Language Statement and consent form with them over them phone and send it to them (either by email or post) to be signed and returned by post or in person. Once the carer has consented, the research assistant will arrange a convenient time (and place) to collect time 1 data either over the phone or in person (at the hospital). Time 1 data collection will take no longer than 30 min to complete and will be conducted within 1 week from referral/admission.

The research assistant will phone the family carer when it is time to collect time 2 and 3 data and ask them if they would prefer to complete the questionnaire over the phone, in person at the hospital, or by post. Times 2 and 3 data collection will take no longer than 30 min to complete.

If the family carer is in the intervention group, the research assistant will refer them to the family meeting facilitator (who has been trained to conduct the structured family meetings) as soon as the carer has completed time1 data. Similarly, once the family meeting has been conducted (ideally within a week of time 1 data being collected) the family meeting facilitator will inform the research assistant. This study design does not allow the research assistant to be blinded to the condition to which carers are allocated.

If the family carer is in the control group, then they receive usual care for the period between time 1 and time 2 data collection.

